## **5. RISK/BENEFIT ASSESSMENT**

### **5.1 *Potential Risks***

Risks of participation in this study are minimal and unlikely to occur given the safeguards in place. Psychological risks include: 1) the possibility that some participants may perceive some questionnaire or background data assessment as intrusive or causing them to feel uncomfortable; 2) breach of confidentiality. The study involves an intervention designed to enhance adherence to standard diabetes care (e.g., adherence to the prescribed diabetes medication, healthy eating, and physical activity behaviors). If our intervention improves adherence to the medication regimen or if participants make lifestyle changes (e.g., increased physical activity), more episodes of blood sugar fluctuation may result. We will advise participants of the importance of monitoring their blood sugar as suggested by their doctors, and to contact their doctors as soon as they experience low blood sugar (<70mg/dl) or high blood sugar (based on the level advised by their doctors, as the upper limit varies between patients/providers). We will report these episodes of low and high blood sugar to Medical Monitor within 2 business days of knowing these events.

This study involves the use of text messages to deliver diabetes video links to participants. There are some security concerns with regard to text messages. We acknowledge these concerns, however, we think the benefits outweigh the risks. These low-income Chinese immigrants are already familiar with using text messaging and it is part of their daily life. Requiring them to download a new app or using a new portal would be extremely challenging due to the limited digital literacy issues in this population. We have used text messages in research studies over the past 5 years and have not encountered any privacy or confidentiality concerns. We have and will continue to work closely with our Medical Center IT department to ensure patient privacy and confidentiality. We will replicate measures used in our prior studies including: 1) assigning a unique code to each participant for accessing the intervention videos; 2) directing participants to refrain from sending any PHI via text messages and to call the study phone number for any questions; 3) study staff will use NYU encrypted study phones, that are HIPAA compliant; 4) all study staff will be trained on how to communicate with patients with regard to text messages.

### **5.2 *Benefits***

Participants may benefit from the DSMES as they may decide to exercise more, make healthy dietary choices, and other lifestyle modifications that may lead to improved diabetes management. Information learned during the study may also produce benefits for future patients by improving their diabetes care.

## **6. CONFIDENTIALITY AND DATA STORAGE**

We will use the IRB recommended RedCap for data storage ([openREDCap.nyumc.org](https://openREDCap.nyumc.org)). We will also work with MCIT to set up a NYU shared network drive which is HIPAA compliant (for offsite backup storage) specifically for our study. All study personnel have already taken the mandatory HIPAA and Patient Privacy/Confidentiality training modules required by our institutional IRBs, to ensure that they are aware of the importance of patient confidentiality and all appropriate laws

regarding protection against privacy breaches. Procedures will be in place to ensure that all files containing subject information will be kept in locked filing cabinets or password-protected electronic databases on a secure server. The majority of study data will be maintained in electronic files with no patient identifiers other than a study ID number; there will be one file maintained separately with its own password protection that links study ID numbers to patient identifying information.

No identifiable information about study participants will be disclosed to individuals outside those approved by the IRB to be on the study protocol. No publications that result from the study will identify individual participants.

The text-message-based video counseling will be protected via password-enabled access. Only study participants will have access codes to open these videos. Others in the same household would not be able to open the video, unless participants choose to share the access code.

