In our prior study, we successfully developed 24 culturally and linguistically tailored DSMES videos. Video links were shared via the free and popular social media platform with 30 Chinese immigrants with T2D. The mean video watch rate was high (92%). In our one-arm feasibility pilot, we found HbA1c at 6 months significantly declined by 0.6% compared to baseline (95% CI: 0.3%-0.9%,  $p=0.001$ ). Chinese immigrants also reported they needed assistance with SDOH barriers to T2D (e.g., lack of insurance, financial barriers to accessing medication or glucose testing strips). Building upon these pilot data, the overall goal of **this R01 study** is to examine the efficacy of the video-based DSMES (hereafter VIDEO), or the video-based DSMES+CHW intervention (hereafter VIDEO+CHW) compared with a wait-list control group (hereafter CONTROL) to improve glycemic control among 405 Chinese immigrants with uncontrolled T2D in NYC. Participants will be randomized with equal allocation to one of the 3 groups. The VIDEO group will receive 1 DSMES brief video/week for 24 weeks delivered via text message. The VIDEO+CHW group will receive the same DSMES videos plus bi-weekly support calls from a CHW for 24 weeks. The CHW will assess participants' SDOH barriers to T2D care and link them to available resources in the community. The CONTROL group will continue to receive their usual care and at the end of the study, they will receive DSMES videos. Measurements will occur at baseline, 6, and 12 months.

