**Sample Size Estimates: Primary Outcome (HbA1c at 6 months):** The primary aim is to examine the efficacy of the VIDEO and VIDEO+CHW interventions on HbA1c (primary outcome) at 6 months. We hypothesize that the VIDEO+CHW group will have the largest reduction in HbA1c, followed by the VIDEO group and then the CONTROL group at 6 months ( $HbA1c_{VIDEO+CHW} < HbA1c_{VIDEO} < HbA1c_{CONTROL}$ ). Based on our preliminary data, we expect to observe a 0.6% difference between the VIDEO and CONTROL groups. Based on data of a prior CHW intervention in Hispanic immigrants with T2D, we expect to see a group difference of 0.4% between the VIDEO+CHW and VIDEO groups. Using the observed  $SD=0.8\%$  of HbA1c in our preliminary study, based on a two-sample two-sided t-test,  $n=86$  (per group) will be required to detect a minimum group difference of 0.4% in HbA1c with a power of 80% and a type I error of 0.0167 (to account for 3 group comparisons). We will abstract HbA1c data from the electronic medical record, which often has a high rate of missing data due to various reasons (e.g., patients miss the A1c appointment or change to a different health care system). Our pilot study achieved 70% completion rate of A1c follow up data. With a conservative rate of 60-65%, we will recruit 405 (135/group) participants to yield a final sample of at least 258 (86/group). We believe a sample of 405 will provide sufficient power to detect significant differences between the three groups (VIDEO+CHW vs. VIDEO; VIDEO vs. CONTROL; VIDEO+CHW vs. CONTROL).

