### **3.3. Characteristics of the Research Population**

To be eligible for the study, participants must: 1) self-identify as a Chinese immigrant or Chinese American; 2) be above 18 years old, 3) have a diagnosis of T2D in the medical record; 4) have had an appointment with a physician for routine T2D care within the past 12 months; 5) have a most recent  $HbA1c \geq 7\%$ ; 6) be willing to receive brief videos regarding T2D management, and 7) possess a smartphone or, if they do not have one, be willing and able to use a study smartphone. Individuals will be excluded from participation if they meet any of the following: (1) unable or unwilling to provide informed consent; (2) unable to participate meaningfully in the intervention (e.g., uncorrected sight and hearing impairment); (3) unwilling to accept randomization assignment; (4) is pregnant, plans to become pregnant in the next 6 months, or becomes pregnant during the study, or (5) is breastfeeding (e.g., they may have potential dietary restrictions).

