##### **4.4.1 Randomization**

The study biostatistician will create a prior randomization sequence using a computer-generated list of random numbers. The independent study staff will inform participants of their group assignment and explain the next step after finishing questionnaires during the baseline phone call.

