##### **4.4.2 Intervention Arms**

**Wait-list control group (CONTROL):** Participants in this group will continue to receive the standard of usual care for their T2D at their doctor's office during the course of our study. At the end of the study, the CONTROL group will be provided the opportunity to receive DSMES videos.

**Video-based DSMES (VIDEO):** Participants in the VIDEO group will receive brief pre-recorded DSMES videos, which include both educational and SCT-based behavioral content. All intervention videos have been linguistically and culturally tailored and pilot tested in a prior study. Similar to the prior study, we will deliver video links via text messages. We will send 1 DSMES video each week for a total of 24 weeks with each video lasting about 5 minutes in duration. Our preliminary data demonstrated high feasibility and acceptability of these DSMES videos.

**Video-based DSMES+CHW (VIDEO+CHW):** Participants in this group will receive the same DSMES videos as described above. In addition, they will also receive brief phone calls from CHWs every 2 weeks during the 24 weeks video program. During these calls, CHWs will assess whether participants need assistance on SDOH barriers (e.g., health insurance enrollment, financial assistance on covering medication/test strips, food assistance). If needed, CHWs will link participants to available services within the community. CHWs will also provide assistance on navigating the complex health care systems and serve as an advocate for patients during doctor visits if needed. These phone calls will be audio recorded for data integrity and quality assurance. We will randomly select phone call audio recordings to ensure that they are following our study protocol. Audio recordings will be password protected and stored on the NYU Langone shared drive which is only accessible to our study team members. We will destroy the recordings in July 2029, one year after our grant ends.

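### Eligibility admits co-residents of enrolled participants and earlier recipients of the same videos, so avoidable cross-arm exposure of modest, unknown size can bias contrasts toward no effect

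*Protocol*

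**What the plan says.** **Eligibility (Protocol 3.3).** The exclusions open with "Individuals will be excluded from participation if they meet any of the following" and run to five items: consent, ability to take part, acceptance of allocation, pregnancy and breastfeeding. None concerns a co-resident already in the trial, and none concerns earlier receipt of the videos.

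**Randomisation (4.4.1).** "The study biostatistician will create a prior randomization sequence using a computer-generated list of random numbers". No household rule is given.

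**Barrier to exposure (5.1 and 6).** Each participant has a unique code to open the videos. Section 6 qualifies this: "Others in the same household would not be able to open the video, unless participants choose to share the access code". The code is presented as a privacy measure. The instruction to participants in 5.1 is about keeping health information out of text messages, not about keeping the code to themselves.

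**CHW component (4.4.2).** "CHWs will assess whether participants need assistance on SDOH barriers (e.g., health insurance enrollment, financial assistance on covering medication/test strips, food assistance").

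**The pilot (2.1 and 4.4.2).** "Video links were shared via the free and popular social media platform with 30 Chinese immigrants with T2D", and "All intervention videos have been linguistically and culturally tailored and pilot tested in a prior study".

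**Sample size (3.2).** For the videos, "we expect to observe a 0.6% difference between the VIDEO and CONTROL groups". For adding the CHW, 0.4% is expected. The full effects are used, and recruitment is inflated only for missing HbA1c.

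**The concern.** CONTROL is meant to go without the videos until the end of the study. Recruitment includes Chinatown clinics, community organisations and senior centres, where two members of one household could both be eligible and be allocated to different arms. Three routes of exposure then stay open.

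- **Shared access code.** A CONTROL participant sees the videos of a co-resident in either video arm. This touches the two contrasts with CONTROL. It cannot touch VIDEO+CHW vs VIDEO, because both of those arms receive the videos anyway.
- **CHW help acting on the household.** Insurance enrolment or food assistance arranged for one person may benefit a co-resident in VIDEO or CONTROL. This is the only route that narrows VIDEO+CHW vs VIDEO.
- **Pilot re-entry.** A pilot participant whose latest HbA1c is still at least 7% can enrol, having already received the videos.

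All three push toward no difference. Intention-to-treat analysis keeps the diluted contrast as it is and cannot restore the undiluted one. Section 3.1 says that CONTROL is there to estimate the effect size of each component, so an underestimate matters even where power is ample.

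**Working it through.** **Inputs from Protocol 3.1 and 3.2.** Differences of 0.6% (VIDEO vs CONTROL) and 0.4% (VIDEO+CHW vs VIDEO); SD 0.8%; two-sided alpha 0.0167; 86 analysed per group; 405 recruited, 135 per arm, equal allocation.

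**Step 1: the plan's own figure.** The standardised difference is 0.4/0.8 = 0.5. A two-sample t-test at 80% power needs 85.2 per group, rounded up to 86. Power at 86 is 80.4%, so the stated figure reproduces. For 0.6%, power at 86 is 99.3%.

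**Step 2: from household pairs to exposure.** Let h be the share of participants enrolled as household pairs. The documents do not give h, so the values below are assumptions. Under equal individual allocation a co-resident lands in any given arm with probability 1/3.

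- VIDEO participants with a co-resident in VIDEO+CHW: h/3.
- CONTROL participants with a co-resident in either video arm: 2h/3.

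**Step 3: from exposure to diluted difference.** Suppose each exposed person gains the full effect of the component reached. This is an upper bound.

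- VIDEO+CHW vs VIDEO: 0.4 × (1 − h/3).
- VIDEO vs CONTROL: 0.6 × (1 − 2h/3). If CHW help also spills over, VIDEO and CONTROL each gain 0.4 × h/3, and this cancels from the contrast.

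| h | People in pairs (of 405) | VIDEO+CHW vs VIDEO | Power at 86 | VIDEO vs CONTROL | Power at 86 |
|---|---|---|---|---|---|
| 0 | 0 | 0.400% | 80.4% | 0.60% | 99.3% |
| 5% | about 20 | 0.393% | 78.9% | 0.58% | 99.0% |
| 10% | about 41 | 0.387% | 77.3% | 0.56% | 98.5% |
| 15% | about 61 | 0.380% | 75.7% | 0.54% | 97.7% |

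VIDEO+CHW vs CONTROL starts at 0.6 + 0.4 = 1.0%. At h = 15% it is 1.0 − 0.6 × 0.10 − 0.4 × 0.05 = 0.92%, which needs 18 per group, so power is not at issue.

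**Step 4: where the reserve runs out.** VIDEO vs CONTROL falls to 0.4%, and so to 80.4% power, when 0.6 × (1 − c) = 0.4, that is when c = 1/3 of CONTROL is fully exposed. With c = 2h/3 this needs h = 50%. VIDEO+CHW vs VIDEO has no reserve, because 86 was set on 0.4%.

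**Step 5: pilot re-entry.** At most 30/405 = 7.4%, or 10 per arm if spread evenly (10/135 = 7.4%). If those in CONTROL counted as fully treated, VIDEO vs CONTROL would be 0.6 × (1 − 0.074) = 0.556%, with power 98.3%.

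**The case against.** The strongest reply is that the exposure is speculative and small. Much of that stands.

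- **There is a safeguard.** Codes are personal, and the quoted sentence is a caveat to that safeguard, not an error or a contradiction. The telephone screener is cited in 4.2 but not shown. This stands in part: a code its holder may share, with no instruction against sharing, is a partial barrier, and the criteria the screener would apply are those in 3.3.
- **Not every contrast is affected by every route.** A reader might infer that shared videos dilute all three comparisons. They do not: VIDEO+CHW vs VIDEO depends only on CHW spill-over, and 4.4.2 describes help to participants without saying that it reaches others.
- **Large losses need extreme pairing.** A reader might assume that 10% or 20% of VIDEO gains the full CHW effect and conclude that power falls to 70% or 58%. With exposure of h/3, those rates need 30% or 60% of all participants (about 122 or 243 of 405) enrolled as pairs. Both members must have T2D with HbA1c of at least 7%. Recruitment also extends to private practices and NYU Langone campuses in Manhattan, Brooklyn and Long Island, which makes incidental pairing less likely.
- **Pilot benefit is already in the baseline.** A reader might count a pilot participant in CONTROL as fully treated within the trial. Section 7.1 estimates change from baseline, so a benefit already present at entry is not gained again. What remains is mainly that such people have less left to gain in the video arms.

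None of this closes the gap in 3.3. It limits its size.

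**Conclusion.** The gap is real and its likely effect is modest. As written, the plan lets co-residents and earlier recipients of the videos be randomised individually, and it acknowledges that the code can be shared. The direction of bias is toward no effect. Its size is unknown because the documents give no rate of household pairs or of code sharing.

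With 5% to 15% of participants in pairs and full transfer of effect, VIDEO+CHW vs VIDEO loses about 2 to 5 percentage points of power. That loss also rests on the inference that CHW help carries over to a co-resident. VIDEO vs CONTROL keeps ample power; the harm there is an estimate low by up to 0.06 percentage points of HbA1c. Pilot re-entry is a minor contributor. The documents do not support reading this as a serious loss of power or a threat to the trial's main conclusion. It is a cheap improvement to the design.

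**What to change.** Add two exclusions to Protocol 3.3 and matching questions to the telephone screener:

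1. a member of the same household is already enrolled (one participant per household);
2. the person has previously received the study's DSMES videos, including in the pilot.

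Also tell participants in the video arms not to share the access code while the trial is running.

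The cost is two eligibility lines, two screener questions and one instruction. A few eligible spouses and at most 30 pilot participants would not be enrolled. Randomising by household, with the clustering allowed for in the analysis, would also address the household routes but is more work. For anyone already enrolled, household links and earlier video exposure can be recorded so that the extent is known.

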## 7. DATA ANALYSIS AND DATA MONITORING

### 7.1 Data Analysis

**Analytic Plan for Aim 1:** An “intent-to-treat” approach will be used to address the specific aims. For Aim 1, we hypothesize that the VIDEO+CHW group will have the largest reduction in HbA1c at 6 months, followed by the VIDEO group, and then the CONTROL group. A random effects linear mixed modeling will be used to test time-specific differences attributable to the intervention. We also will use the “lincom” command in Stata to estimate differences in time-specific changes from baseline. Randomization should obviate the need for adjustment, but in the case of unbalanced baseline covariates, these will be included as necessary in adjusted analyses. We will use splined linear mixed models with repeated measures to compare changing trends in different periods: 0-6 months and 6-12 months. In this analysis, we will adjust for the covariates as needed.

**Analytic Plan for Aim 2:** For Aim 2, we hypothesize that the VIDEO+CHW group will have the greatest improvements in secondary patient-centered outcomes. Similar to the plan for Aim 1, we will use random effects linear mixed models, adjusting for relevant covariates in the case of unbalanced covariates between the treatment arms at baseline. We will use splined linear mixed models with repeated measures to compare changing trends in different periods, adjusting for the covariates as needed.

**Analytic Plan for Aim 3:** For exploratory Aim 3, we hypothesize that the VIDEO+CHW group will have the largest reduction in HbA1c at 12 months. Similar to the plan for Aim 1, we will use linear mixed effects models and splined linear mixed models with repeated measures to compare changing trends in different periods, adjusting for relevant covariates if needed.

**Analytic Plan for Aim 4.** Utilizing the RE-AIM framework, we will address “reach” by comparing demographic and clinical characteristics of patients enrolled vs. eligible and not enrolled, using Wilcoxon’s rank-sum test or Fisher’s exact test. We will also examine these factors separately by sex and age brackets. To address “effectiveness”, we will use the random linear mixed modeling to examine whether the VIDEO+CHW intervention group had a greater reduction than the CONTROL group. For “adoption”, we will use Chi-square tests to compare the proportion of patients completing intervention components. To address “implementation”, we will report the frequency of barriers/facilitators to implementation, as well as other fidelity measures, and Chi-

square tests to compare proportions. Finally, both “implementation” and “maintenance” will be explored qualitatively as described below.

Barriers and facilitators to implementation of the VIDEO+CHW intervention. All interviews will be audio-recorded and transcribed. We will use “constant comparison” analytic approach. The “constant comparison” approach is a method of explanation building in which the findings of an initial case are compared to a provisional category, revised as necessary and then other details or new cases are then compared against the revision and revised again as needed. This process is continued until an area of interest is fully explicated, reaching theoretical saturation. Using “thematic” coding, we will develop an initial set of codes, which will be reviewed by the Steering Committee to ensure they are relevant and complete. For each core code, we will ultimately develop one or more “secondary codes” that represent either more specific or restricted aspects of the phenomenon, to contextualize it, or to suggest underlying meanings. The secondary codes will vary in specificity or subtlety depending on the judged substantive value of additional refinements. Transcripts will be coded by at least four coders (graduate and post-doctoral students). Discrepancies in coding will be discussed and resolved, then the process is repeated with a new set of transcripts until an acceptable level of inter-coder reliability between them has been achieved, estimated using an appropriate chance-corrected statistic (e.g., kappa for nominal data and T-index for ordinal data). We will use Atlas.ti software to analyze the transcripts.

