**Table 2: RE-AIM and CFIR Evaluation Frameworks**

| CONSTRUCTS                                                                                                                                   | MEASURES (Quantitative/Qualitative)                                                                                                                                                                                               | DATA SOURCES                                                                                                    | TIME FRAME                                                                      |
|----------------------------------------------------------------------------------------------------------------------------------------------|-----------------------------------------------------------------------------------------------------------------------------------------------------------------------------------------------------------------------------------|-----------------------------------------------------------------------------------------------------------------|---------------------------------------------------------------------------------|
| REACH: What % of the target population came into contact with the program? Were participants representative of the target population? |                                                                                                                                                                                                                                   |                                                                                                                 |                                                                                 |
| Participants                                                                                                                                 | 
 
% patients with uncontrolled T2D
 
% patients at risk who received the VIDEO+CHW intervention
 
Representativeness of patients referred and participated in study
 
 | 
 
EHR data
 
In-depth interviews with providers and CHWs
 
 | 
 
Baseline, 6 months, 12 months
 
 |

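### Reach asks how representative participants are, but the protocol names only significance tests for that comparison, and their result depends on group size as well as on the difference

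*Protocol*

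**What the plan says.** Table 2 (Aim 4 Implementation Evaluation) frames Reach partly as a question of representativeness: "Were participants representative of the target population". One of its measures is "Representativeness of patients referred and participated in study", listed without a metric. The other Reach measures are percentages, such as the share of "patients at risk who received the VIDEO+CHW intervention".

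Section 7.1, Analytic Plan for Aim 4, gives the method. Reach is addressed by "comparing demographic and clinical characteristics of patients enrolled vs. eligible and not enrolled", "using Wilcoxon’s rank-sum test or Fisher’s exact test". The next sentence adds: "We will also examine these factors separately by sex and age brackets".

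For this comparison the protocol states no effect measure, confidence interval, significance level or margin for a material difference. It does not give the number of eligible patients who do not enrol, and it does not define the age brackets.

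**The concern.** Whether participants represent the target population is a question about how far the enrolled differ from the rest, and in what. A test of no difference asks something else. Section 4.1 recruits through posters, provider referral and record searches, so the enrolled are not a random draw from the eligible, and exact equality is not a plausible state to test. Whether a given imbalance reaches significance then depends heavily on how many people stand on each side.

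This matters most when the overall comparison is set beside the look by sex and age. The overall comparison has 405 enrolled patients, while an age bracket may have a few dozen. If the same tests are used in both, one and the same imbalance can be significant overall and non-significant in a bracket through numbers alone. Someone deciding whom the programme reaches, with a view to scaling it, could be misled by the non-significant result.

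**Working it through.** **The plan's own figure.** The protocol gives no sample-size or power figure for Reach. Its only such figure is for HbA1c: 86 per group "to detect a minimum group difference of 0.4% in HbA1c with a power of 80% and a type I error of 0.0167" (section 3.2). With SD 0.8% the standardised difference is 0.4/0.8 = 0.5. A two-sided two-sample t-test at alpha 0.0167 and 80% power needs 85.2 per group, rounded up to 86, so the figure reproduces. It does not bear on Reach, which compares different groups.

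**Inputs for Reach.**
- Enrolled: n1 = 405 (section 3.2). The 258 expected to have HbA1c data is not the relevant number, because Reach compares who enrols.
- Eligible and not enrolled: not stated. Assumed range n2 = 500 to 10,000.
- Significance level: not stated for Reach. Assumed two-sided 0.05.
- Age bracket: not defined. Assumed 40 enrolled, about a tenth of 405, with a proportional comparison group (n2 × 40/405, about 50 to 1,000).

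**Formulas** (normal approximation). SE = sqrt(1/n1 + 1/n2). The smallest observed standardised difference that is significant is 1.96 × SE. Power at a true difference d is Φ(d/SE − 1.96) + Φ(−d/SE − 1.96).

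**Smallest significant observed difference.**

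| Not enrolled, overall | 405 enrolled | Bracket of 40 enrolled |
|---|---|---|
| 500 | 0.131 | 0.417 |
| 2,000 | 0.107 | 0.340 |
| 10,000 | 0.099 | 0.316 |

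**Power at a true difference of 0.2.**
- 405 vs 500: SE = 0.0669, 0.2/SE = 2.99, power 85%.
- 405 vs 10,000: SE = 0.0507, 0.2/SE = 3.95, power 98%.
- 40 vs about 50: SE = 0.213, 0.2/SE = 0.94, power 16%.
- 40 vs about 1,000: SE = 0.161, 0.2/SE = 1.24, power 24%.

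In the bracket, a difference of 0.2 would be non-significant 76-84% of the time.

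**Check with the named tests.** This uses the Wilcoxon efficiency of 3/π and assumed pools of 405 to 5,000 not enrolled. Power at 0.2 is 79-97% overall, 50-76% within one sex (half the sample), 28-47% in an age quarter, 14-22% in a tenth and 10-14% in a twentieth. For Fisher's test, simulated with a reference proportion of 50%, a 10-point difference is significant 96% of the time with 405 vs 2,000 and 23% of the time with 50 vs 250. Both tests show the same gradient.

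**How far it goes.**
- Overall, a true difference of 0.1 has power of 29-47% for pools of 405 to 5,000, and about 50% at most with an unlimited pool, because enrolment stops at 405. At 0.05, power is 11-17%.
- A true difference of 0.5 has essentially 100% power within one sex and at least 94% in an age quarter. In a sex-by-age cell of about 51 enrolled it has 69-92%, and in a twentieth (about 20 enrolled) 34-56%.

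**What an interval gives instead.** The 95% half-width for a standardised difference is about 0.14 (405 vs 405), 0.11 (405 vs 2,000) and 0.10 (405 vs 5,000). In a bracket of 40 it is 0.32-0.42. The estimate does not change systematically with group size; only its precision does, and the interval shows it.

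**The case against.** The case for leaving the text alone has several parts, and much of it stands.

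- **No decision rule is stated.** The protocol does not say that a significant result means unrepresentative, or that a non-significant one means representative. Comparing characteristics normally involves tabulating them, so readers would probably see the size of the differences. This stands. A reader might infer that the Reach conclusion will point the wrong way, but the protocol does not commit anyone to that reading.
- **Reach does not rest on tests alone.** Table 2 also lists percentages and interviews with providers and CHWs. This is true, but the percentages measure coverage and burden, and neither source is given as the method for comparing enrolled with non-enrolled patients.
- **The subgroup sentence names no test.** It says only that the factors will be examined by sex and age. This is correct, so the bracket figures are conditional on the same tests being used there. The sentence directly follows the one naming the tests, and no other method is offered.
- **Stronger claims fail.** A reader might infer that trivial differences will be flagged overall and large ones missed by sex and age. The calculations do not support this. A true difference of 0.1 is at best an even chance overall, and large differences are not missed by sex. They are at real risk only in small age brackets or sex-by-age cells, which the protocol does not define.
- **This could be left to the SAP.** A SAP, not available here, might add effect sizes. But the protocol does not leave the method open: it names one, and that method fits its question poorly.

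**Conclusion.** The point holds in a limited form. For representativeness, the protocol names only hypothesis tests, and these do not measure the quantity Table 2 asks about. A standardised difference of 0.2 would be significant about 85-98% of the time with 405 enrolled. If the same tests were applied in a bracket of about 40 enrolled, it would be significant about 16-24% of the time. Non-significance in such a bracket says little about representativeness.

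The 405 comes from the protocol. The number not enrolled (500 to 10,000), the bracket size, the two-sided 5% level and the use of tests within brackets are assumptions. The gradient from large to small groups does not depend on the exact values chosen.

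The consequence is minor. It concerns how one descriptive part of Aim 4 is read, and leaves the primary and secondary efficacy analyses untouched.

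**What to change.** In section 7.1, Analytic Plan for Aim 4, state that the Reach result is the set of standardised differences, or differences in medians or proportions, between enrolled and eligible-not-enrolled patients. Give each with its 95% confidence interval, overall and by sex and age bracket. Base the conclusion on these estimates and intervals. The Wilcoxon and Fisher p-values may stay as secondary information.

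Do not require every bracket to pass a fixed margin. With a half-width of 0.32-0.42, the interval in a bracket of 40 enrolled could never lie wholly within ±0.2. Such brackets should be reported as inconclusive.

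The cost is about one sentence of protocol text, using the data the planned tests already need. The small downside is that wide intervals in small brackets will be visible and must be described as such.
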